**ABSTRACT**

**BACKGROUND**

Mojeaga^®^ (a special blend of *Alchornea, Pennisetum, and Sorghum extracts*) may be very effective in correcting anemia in gynecological and obstetrics patients. Limited available studies in patients suggest a seemingly high efficacy but provide little information on benefits and adverse events. Study on its use in treatment of iron deficiency anemia in adult patients who are intolerant to oral iron preparations or who refuse blood transfusion is highly desirable. To our knowledge, there is no prior randomized trial on the effectiveness of Mojeaga when co-administered with oral iron therapy schedule for correction of anemia in Obstetrics and gynecology practice.

**OBJECTIVES**

To determine the efficacy, safety and tolerability of Mojeaga as adjunct to conventional oral iron therapy for correction of anemia in puerperal and obstetrics patients.

**METHODS**

A pilot open-label randomized clinical trial will be conducted in patients with confirmed diagnosis of anemia (<10.0 g/dl) in Obstetrics and gynecological Clinics of Nnamdi Azikiwe University Teaching Hospital, Nnewi. All laboratory parameters will be carried out at Nnamdi Azikiwe University Teaching Hospital, Nnewi, laboratory and other collaborating hospitals by [name] and [name]. Eligible patients will be randomized to either Mojeaga 50 mls to be administered three times daily in conjunction with iron therapy Astyfer one capsule two times daily for 2 weeks or conventional iron therapy alone (Astyfer one capsule two times daily) without Mojeaga for 2 weeks. Repeat hemoglobin/hematocrit level will be done 2 weeks post-initial therapy. Primary outcome measures will be changes in the hematocrit level at two weeks after initial therapy and mean or median hematocrit level at two weeks after initial therapy. Secondary outcome measures will include incidence of disappearance of any previously existing anemic symptoms, and presence and incidence of any adverse events. Analysis will be by intention-to-treat.

#### TRIAL REGISTRATION: Pan Africa Clinical Trial Registry PACTR201901852059636.

**INTRODUCTION**

Anemia in women is a major public health burden worldwide, particularly in low- and middle-income countries, including Nigeria [1]. According to the World Health Organization, anemia affects approximately 2 billion people worldwide, which results in an estimated global prevalence of almost 25% [2]. The World Health Organization (WHO) estimates the prevalence of anemia among pregnant women to vary from 53.8% to 90.2% in developing countries, and 8.3–23% in developed countries.

Anemia impacts upon more than half the preschool children and pregnant women in developing countries and at least 30%–40% in developed countries [2]. Additionally, a high prevalence of anemia is associated with the elderly and with acute as well as chronic conditions. The World Health Assembly has set a target of a 50% reduction in anemia among women of reproductive age by 2025 [1].

Although several factors such as vitamin deficiencies (A, B12, folic acid), infectious diseases (parasites), chronic inflammation, and genetic disorders may cause anemia, iron deficiency is undoubtedly the most common cause of anemia worldwide [3]. Notably, iron deficiency affects not only red blood cell production but also cellular functions related to muscle metabolism, mitochondrial function, neurotransmitters, DNA synthesis, and the immune system [4, 5]. For example, throughout pregnancy, total iron requirements increase to meet the major hematologic changes of the mother and the increasing demands of the growing fetus [6]. Iron deficiency anemia (IDA) during pregnancy is associated with an increased risk of preterm birth, low birthweight, fetal growth restriction, and increased neonatal and maternal mortality. Furthermore, iron deficiency may predispose a person to postpartum IDA, peripartum blood transfusion, infections, and precipitate heart failure [6].

IDA is often treated with oral iron supplement even in pregnancy. However, due to gastrointestinal side effects such as nausea, vomiting, and constipation, compliance is often poor and results in subsequent discontinuation [4, 6, 7]. As such, intravenous iron administration or blood transfusion is increasingly being recommended for women who are non-compliant with oral iron, have severe IDA, or those who require rapid intervention [6]. However, intravenous drug administration have been infrequently utilised in clinical practice due to undesirable adverse reactions, including severe allergic reactions and anaphylaxis. Blood transfusion is not without complications and some religious groups object to blood transfusions.

Mojeaga^®^ (produced by Mojeaga International Ventures Ltd, Nigeria) is a natural preparation containing a combined *Alchornea*, *Pennisetum*, and *Sorghum* extracts [8,9]. It contains free organic oral iron preparation among other nutrients that allows co-administration of conventional hematinics or other iron preparations. Mojeaga has been approved by the National Agency for Food and Drug Administration and Control (NAFDAC) with NAFDAC registration number of A7-0996L. The *Pennisetum* extract and *Sorghum* extract in Mojeaga are excellent sources of iron, potassium, flavonoids and other phytonutrients. According to the manufacturers, Mojeaga works by promoting healthy metabolic processes because it contains high levels of B-group vitamins [8, 9]. Mojeaga also works by effectively mopping up the free radicals and reactive oxygen species, and quickly reverse the lipid peroxidative and cellular damages. It increases the levels of packed cell volume and hemoglobin and contains antioxidants and natural minerals. It also has strong anti-inflammatory property and enhances general body metabolism. It builds immune system, and it is high in natural iron [8, 9]. There is an additional major benefit of the Mojeaga, in that it can be administered in relatively high normal doses in a short period of time [10].

In one recent report, anemic pregnant women of gestational age of 36 weeks with IDA of hemoglobin level of 5g/dl received Mojeaga in addition with oral iron therapy (adjunct therapy) for two weeks, and had their hemoglobin appreciated to 10 g/dl two weeks after treatment without any adverse pregnancy outcome or neonatal outcome [8]. In other published reports, significantly higher number of women achieved anemia correction within a shorter time frame, and there were markedly fewer gastrointestinal treatment-related adverse events especially when the drug is administered in sips [9, 10, 11]. This lends support to the hypothesis that Mojeaga in combination with oral iron therapy is superior to oral iron therapy alone for correcting anemia in gynecological and obstetrics patients.

To our knowledge, this is the first randomized study that will be reporting on efficacy and safety of combined Mojeaga and oral iron therapy schedule. Therefore, this proposed study is aimed at determining the effectiveness, safety and tolerability of Mojeaga as adjunct to conventional oral iron therapy for correcting anemia in gynecological and obstetrics patients.

**AIMS AND OBJECTIVES**

**AIM:** To determine the efficacy and safety of Mojeaga on puerperal and obstetrics patients with diagnosis of anemia, in NAUTH, Nnewi, south-eastern Nigeria.

**SPECIFIC OBJECTIVES**

- 1. To determine the mean hemoglobin/change in hematocrit level following combined Mojeaga and conventional iron therapy among puerperal and obstetrics patients diagnosed with anemia compared with that of those with conventional iron therapy alone.
  2. To determine the proportion of disappearance of anemic symptoms following combined Mojeaga and conventional iron therapy among puerperal and obstetric patients diagnosed with anemia compared with that of those with conventional iron therapy alone.
  3. To determine the proportion of maternal adverse events following combined Mojeaga and conventional iron therapy among puerperal and obstetric patients diagnosed with anemia compared with that of those with conventional iron therapy alone.

**OUTCOME MEASURES**

**PRIMARY**

1. Mean or median hematocrit level at two weeks after initial therapy.
2. Changes in the hematocrit level at two weeks after initial therapy.

**SECONDARY**

1. Proportion of patients with persisting anemic symptoms (weakness, easy fatigability) at two weeks after initial therapy.
2. Incidence of any maternal adverse events (such as diarrhea, nausea, vomiting and colitis) following commencement of therapy.
3. Incidence of any fetal adverse events (such as preterm labor or jaundice) following commencement of therapy.
4. Mean levels of renal function parameters (serum electrolyte, urea and creatinine) at two weeks after initial therapy.
5. Mean levels of liver function parameters (AST, ALT and ALP) and lipid profiles at two weeks after initial therapy.

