**Study population**

The participants will comprise both obstetrics and puerperal adult patients with clinical and laboratory diagnosis of anemia and who will be give written informed consent before recruitment. The patients will be recruited at the outpatient clinic or antenatal clinics or referred for treatment of their anemia, in the hospital.

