**Inclusion criteria**

Both obstetrics and puerperal adult patients with confirmed clinical and laboratory diagnosis of anemia (<10.0 g/dl) and with normal liver and renal function markers or profiles will be included.

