**Non maleficence to participants**

There is insufficient data (except those from the manufacturer) to guarantee absence of any undesired effect.

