**FETAL/NEONATAL OUTCOME during therapy**

1. **Preterm labour** a.) YES----b.) NO------
2. **Preterm PROM** a.) YES----b.) NO------
3. **Birth weight (kg)----------------------------**
4. **Birth anomaly---------------**

**PROFORMA: Efficacy and safety of Mojeaga® in combination with conventional oral iron therapy for correcting anemia in gynecological and obstetrics patients: a pilot randomized clinical trial in NAUTH, Nnewi.**

**NAME OF DOCTOR................................................CODE NUMBER OF PATIENT………………………**

(1). COMPUTER NUMBER OF PATIENT..........................(2) GENDER…………………………

(3). DATE OF RECRUITMENT......................(4) TIME..................(5) AGE.......................

(6.) Marital status: Married [ ] [single [ ] Divorced [ ](7.) LMP………..(8)GESTATIONAL AGE..............

(9). Parity.................(10). Body weight-.............(11). Height: (cm)......................................................

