**FETAL/NEONATAL OUTCOME during therapy**

1. Preterm labour a.) YES—-b.) NO—-

2. Preterm PROM a.) YES—b.)NO-----

3. Birth weight (kg)----------------------------

4. birth anomaly

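### Secondary outcome 3 names jaundice and enrols puerperal women, but no form field or scheduled question captures infant events after birth, and its denominator is undefined

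*Combined protocol and SAP*

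**What the plan says.** The Inclusion criteria admit "Both obstetrics and puerperal adult patients" with anemia, and Study population says the same. Breastfeeding is not among the Exclusion criteria and is not recorded on the proforma.

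Under Outcome Measures, the only secondary outcome that concerns the child is the third: "Incidence of any fetal adverse events (such as preterm labor or jaundice) following commencement of therapy". The matching safety objective is maternal only: "To determine the proportion of maternal adverse events following combined Mojeaga and conventional iron therapy among puerperal and obstetric patients".

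The proforma is printed twice. Both copies have a section headed "FETAL/NEONATAL OUTCOME during therapy" with the same four items: preterm labour, preterm PROM, birth weight and birth anomaly.

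Follow-Up describes weekly contacts, a paper on which patients note side effects or adverse events, questions about such events at each interview, and repeat blood tests on the participants. It schedules no question about, or assessment of, an infant. Statistical Analysis gives no denominator for outcome 3.

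On what is known of the product, the section Non maleficence to participants states: "There is insufficient data (except those from the manufacturer) to guarantee absence of any undesired effect".

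**The concern.** A woman who enters after delivery has no fetus from that pregnancy. An outcome labelled fetal does not fit her, and every child item on the form describes something that was over before her first dose. A woman who enters pregnant and delivers during the two weeks of therapy has the same problem from the day of birth: her infant may become jaundiced, and the form has nowhere to record it.

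Two things are at stake. First, a listed safety outcome names an event that the data collection form cannot hold, so its incidence cannot be reported reliably. Second, if all randomised women form the denominator, those who cannot have the event lower the reported rate. The trial aims to assess safety in puerperal as well as obstetric patients, and the section Beneficence to participants presents it as the groundwork for a full trial, so a gap in the form is likely to be carried forward.

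**Working it through.** **Step 1. Set outcome, form and follow-up side by side.** The plan gives no figure to reproduce here, so the check is whether each instrument can record an event in an infant already born.

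| Place | What it holds | Can it record a post-birth infant event? |
|---|---|---|
| Secondary outcome 3 | Fetal events; preterm labor and jaundice as examples | In part: jaundice is normally seen in a newborn, but the label is fetal |
| Proforma, preterm labour | Event of pregnancy | No |
| Proforma, preterm PROM | Event of pregnancy | No |
| Proforma, birth weight | Fixed at delivery | No |
| Proforma, birth anomaly | Present at delivery | No |
| Follow-Up, diary and interview | Open-ended adverse events reported by the patient | Only if the mother raises it |
| Follow-Up, two-week tests | The participant's own blood | No |

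All four child fields are pregnancy or birth items. None of the four can record an infant event after maternal exposure in a woman enrolled postpartum. Jaundice, named in the outcome, has no field in either copy of the form.

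**Step 2. Denominator.** Let p be the share of women in an arm randomised after delivery and r the fetal event rate among those pregnant. If all women are counted, the reported rate is r × (1 − p). Take r = 10% (assumption) and about 40 evaluable women per arm, from the Sample size section: 47 × (1 − 0.15) = 39.95.

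- 10 of 40 puerperal: 10% × 0.75 = 7.5%
- 15 of 40 puerperal: 10% × 0.625 = 6.25%
- 20 of 40 puerperal: 10% × 0.50 = 5%

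The relative risk, which is the plan's stated measure for categorical outcomes, is multiplied by (1 − p in the Mojeaga arm) / (1 − p in the control arm). It is unchanged if the shares are equal and shifts if they differ. No stratification by pregnancy status is described.

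**Step 3. What collected infant data could show.** With no events in n infants, the exact two-sided 95% upper limit is 1 − 0.025^(1/n):

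- n = 20: 1 − 0.025^(1/20) = 16.8%
- n = 15: 1 − 0.025^(1/15) = 21.8%
- n = 10: 1 − 0.025^(1/10) = 30.8%

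The values of n are illustrations, because the plan does not give the puerperal share.

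**The case against.** The strongest reply is that the plan does not ignore the infant. Outcome 3 covers any such event and names jaundice, the form section has neonatal in its heading, and the diary and interview are not confined to the woman's own symptoms. A reader might infer that infants of puerperal women would yield no safety information whatever. The documents do not support that: a mother could report an infant event by the open route. What remains is that such reports would be incidental, without a defined question, assessment time or denominator, in a trial where patients and staff know the allocation.

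A reader might also infer that birth weights and anomalies from before enrolment would be counted as effects of therapy and blur the comparison. That is not what the plan says. Neither is a listed outcome, outcome 3 is limited to events after treatment starts, and the form heading is limited to the therapy period. The form does nothing to prevent the mistake, so one clarifying sentence is worthwhile, but the error is not planned. Nor does the plan undertake to report child safety for the pooled trial; its safety objective is maternal.

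It can also be said that this is a pilot with a hematocrit primary outcome, and that 10 to 20 infants per arm will settle nothing. Both are true. They limit the weight of the point, but do not explain why a listed outcome lacks a field.

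**Conclusion.** The point holds in a bounded form. Infant events after maternal exposure have no defined or systematic collection, whether the woman was puerperal at entry or delivered during therapy. Jaundice is named as an outcome but has no field. Women randomised after delivery cannot have a fetal event, and nothing removes them from the denominator.

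The size depends on an unstated puerperal share. At one half, a 10% fetal event rate would appear as 5% if all women were counted, and about 20 infants per arm would lack systematic observation. Even if they were observed and had no events, rates up to 16.8% could not be excluded, so the added data would be descriptive only.

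Infant exposure through breast milk is an assumption, since feeding is not recorded. The primary hematocrit comparison is unaffected. The correction should be made because it is cheap and a listed safety outcome cannot otherwise be reported properly.

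**What to change.** Split outcome 3 in two.

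- **(a) Fetal and birth events**, with women pregnant at randomisation as the denominator.
- **(b) Infant events** in any participant with a living infant during the therapy period, including women who deliver during therapy, counted from the later of first dose or birth to the two-week visit.

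Add a jaundice field and a few yes/no infant items to the proforma and to the weekly contacts already planned: breastfed, jaundice, vomiting or diarrhea, feeding problem, unplanned medical attendance. Report counts by arm with exact two-sided 95% intervals and describe them as descriptive. State that birth weight and birth anomaly are not outcomes of therapy for women randomised after delivery.

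The cost is a little more data entry and a minor update of the form and of the consent to cover infant data. No extra visits, staff or procedures are needed.

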**Follow-Up**

The trial is expected to last for at least 16 months. Recruitment will be within the first 6 months of commencement of the study and the follow up will be for at least 10 months from recruitment (ie total of 16 (6+10) months). All participants will be followed up in outpatient settings. During each follow-up weekly visit, patients will be contacted on phone on weekly basis to assess level of compliance. The patients will also be encouraged to record any side effects or adverse events in a paper that will be reviewed at each follow-up visit, and they will be explicitly asked about such events during each interview. The drug compliance will be checked before follow-up test. Any patient found to be developing complications such as worsening of the

symptoms from the study will be given appropriate treatment. Repeat hemoglobin level will be done 2 weeks post initiation of treatment in all the participants to confirm success of treatment (correction of anemia and levels of hemoglobin/hematocrit levels) and absence of adverse effects. All the pre and post (repeat) hemoglobin/hematocrit level will be carried out by hematologist: [name], while the LFT, Lipid profiles and SEUCR will be carried out by the Senior laboratory Scientist of Chemical Pathology- [name] in Nnamdi Azikiwe University Teaching Hospital, Nnewi laboratory.

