16. MARITAL STATUS

1. Single [ ] (b) Married [ ]

17. FINDINGS AT CLINICAL EXAMINATION before therapy…………?**TICK [√] below:**

| **VARIABLE before therapy** | **PRESENCE** | **ABSENCE** |
| --- | --- | --- |
| Epigastrric pain |  |  |
| Nausea |  |  |
| Vomiting |  |  |
| Dizziness |  |  |
| Weakness |  |  |
| Hematemesis |  |  |

18. FINDINGS AT CLINICAL EXAMINATION AFTER therapy……………?**TICK [√] below:**

| **VARIABLE AFTER therapy** | **PRESENCE** | **ABSENCE** |
| --- | --- | --- |
| Epigastrric pain |  |  |
| Nausea |  |  |
| Vomiting |  |  |
| Dizziness |  |  |
| Weakness |  |  |
| Hematemesis |  |  |

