**19. SOME LABORATORY PARAMETERS**

| **LABORATORY VARIABLE** | **VALUES BEFORE THERAPY** | **VALUES AFTER THERAPY** | **NORMAL RANGES** |
| --- | --- | --- | --- |
| Na |  |  |  |
| K |  |  |  |
| Bicarbonate |  |  |  |
|  |  |  |  |
| AST |  |  |  |
| ALP |  |  |  |
| ALT |  |  |  |
|  |  |  |  |
| PCV/hematocrit |  |  |  |
| Hb |  |  |  |
| Wbc |  |  |  |
| Platelets |  |  |  |
|  |  |  |  |
|  |  |  |  |
|  |  |  |  |
|  |  |  |  |

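### The case record form does not match the declared secondary outcomes: 7 of 15 named items have no labelled field, and the fetal block covers a shorter window than the outcome

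*Combined protocol and SAP*

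**What the plan says.** The list of secondary outcomes has five entries. The relevant ones are:

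- Symptoms: "Proportion of patients with persisting anemic symptoms (weakness, easy fatigability) at two weeks after initial therapy".
- Maternal safety: "Incidence of any maternal adverse events (such as diarrhea, nausea, vomiting and colitis) following commencement of therapy".
- Fetal safety: "Incidence of any fetal adverse events (such as preterm labor or jaundice) following commencement of therapy".
- Renal: "Mean levels of renal function parameters (serum electrolyte, urea and creatinine) at two weeks after initial therapy".
- Liver and lipids: AST, ALT, ALP and lipid profiles at the same two-week point.

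The proforma appears twice, with the same clinical, laboratory and fetal content each time. Its laboratory table, headed "SOME LABORATORY PARAMETERS", has labelled rows for sodium, potassium, bicarbonate, AST, ALP, ALT, hematocrit, hemoglobin, white cells and platelets, plus six blank rows. Its clinical table, under "VARIABLE AFTER therapy", offers presence or absence of epigastric pain, nausea, vomiting, dizziness, weakness and hematemesis. Its last block, "FETAL/NEONATAL OUTCOME during therapy", asks for preterm labour, preterm rupture of membranes, birth weight and birth anomaly.

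The Follow-Up section plans weekly telephone contact, a patient-held paper for side effects that is reviewed at visits, direct questioning about events, and laboratory measurement of liver function, lipids and SEUCR. It also says that "the follow up will be for at least 10 months from recruitment". Treatment lasts two weeks (Study Procedure/Drug Administration).

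**The concern.** The form is the only structured record in the documents, and it departs from the outcome list in three ways.

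First, some declared measurements have no labelled place. This also touches eligibility: the inclusion criterion requires normal renal markers, yet the pre-treatment column has no labelled row for urea or creatinine.

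Second, the maternal outcome is an incidence from the first dose, but the form records status at a single examination after treatment. A woman whose nausea resolved before that examination would be ticked absent. The form asks for no onset date and does not ask whether the drug was stopped. In an open-label trial, events noted outside a standard field may also be reported differently in the two arms.

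Third, the fetal heading limits recording to the two treatment weeks, whereas the outcome runs from commencement with no end date.

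Safety is part of the stated aim. The section on non-maleficence concedes that, apart from the manufacturer's data, there is too little information to rule out undesired effects. Under-recording would therefore tend to make a product given in pregnancy look safer than the trial has shown.

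**Working it through.** No figure in the plan needs reproducing here. The check is a match of every item named in the secondary outcomes against the labelled fields of both proforma versions.

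| Outcome | Items with a labelled field | Items without | Covered |
|---|---|---|---|
| Symptoms | weakness | easy fatigability | 1 of 2 |
| Maternal events | nausea, vomiting | diarrhea, colitis | 2 of 4 |
| Fetal events | preterm labour | jaundice | 1 of 2 |
| Renal | electrolytes | urea, creatinine | 1 of 3 |
| Liver and lipids | AST, ALT, ALP | lipid profile | 3 of 4 |

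Covered: 1 + 2 + 1 + 1 + 3 = 8. Named: 2 + 4 + 2 + 3 + 4 = 15. Not covered: 15 − 8 = 7. No outcome is fully covered and none is wholly uncovered. Of the seven, four are named outright (urea, creatinine, lipid profile, easy fatigability). The other three (diarrhea, colitis, jaundice) illustrate a category of any adverse event, and neither version has a line for other events.

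**Time windows side by side**

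- Maternal events: the outcome counts from commencement; the form records one examination after treatment.
- Fetal events: the outcome counts from commencement with no end; the form's heading gives two weeks; the form's own birth weight and anomaly items can be completed only at delivery; planned follow-up is at least 10 months.

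**Share of births outside a literal two-week window**

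The documents give no distribution of gestational age at entry. Assume entry is uniform from week *g* to week 40 and every woman delivers at week 40. The share delivering within two weeks of entry is then 2 / (40 − *g*).

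| Entry range (assumed) | Born inside window | Born outside |
|---|---|---|
| Weeks 14–40 | 2/26 = 8% | 92% |
| Weeks 28–40 | 2/12 = 17% | 83% |
| Weeks 34–40 | 2/6 = 33% | 67% |

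Most births fall outside the window in all three cases.

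**Denominator for fetal rates**

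The trial enrols puerperal women, who cannot have preterm labour. The form offers only yes or no for that item, and the Statistical Analysis section does not say who is counted. If all participants were counted, the rate would be (1 − *p*) times the rate among pregnant women, where *p* is the puerperal share. For *p* of 25%, 50% or 75% (assumed), that gives 75%, 50% or 25% of it.

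**The case against.** The strongest reply is that the proforma is not the only source of data. The patient paper, the weekly calls and the direct questioning exist to catch events that come and go. SEUCR and lipids are to be measured, so values should exist in laboratory records, and the table has blank rows to take them. Diarrhea, colitis and jaundice are examples rather than separately declared outcomes. The birth weight and anomaly items suggest that the fetal block is meant to be completed at delivery under a loosely worded heading.

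Much of this stands. A reader might infer that the safety objectives cannot be answered, that renal function and lipids cannot be compared, or that transient events go uncounted. The documents support none of these. The only safety item among the specific objectives is maternal adverse events, and that has a second route of capture. A reader might also infer that puerperal women will dilute the fetal rates, but no section says that all participants will be counted. If they were, and the puerperal share were balanced between arms, the relative risk would be unchanged; only absolute rates and differences would shrink.

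What the reply does not remove is the mismatch. Patients are only encouraged to use the paper, and the form has nowhere to transcribe it or the interview answers. Unlabelled rows leave entry to the person completing the form, possibly at several collaborating hospitals. Jaundice has neither a field nor any described neonatal assessment. Even if the heading is loose, it contradicts the outcome definition, and staff completing the form will follow the heading.

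**Conclusion.** The concern holds as an inconsistency between form and protocol that puts the secondary outcomes at risk of incomplete or inconsistent capture. It does not show that the safety questions are lost. The firm part needs no assumption: 7 of 15 named items lack a labelled field, there is no open adverse-event line, the maternal tick does not measure incidence since the first dose, and the fetal heading conflicts both with its outcome and with its own items. Fetal outcomes are the weakest part, because no other route of capture is described for them.

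The size of the fetal loss is conditional. The range of 67% to 92% of births missed rests on a literal reading of the heading, uniform entry and delivery at week 40. The denominator is an unstated choice rather than a demonstrated error. The hematocrit primary outcomes are unaffected. The form should be corrected before it is used.

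**What to change.** Revise the proforma and add two sentences to the protocol.

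- Add labelled rows for urea, creatinine and lipids, and fields for easy fatigability, diarrhea, colitis, neonatal jaundice and any other event.
- For adverse events, replace the post-treatment tick with any occurrence since first dose, with onset date and whether the drug was stopped (yes/no). Transcribe it from the weekly contacts and the patient paper for every randomised woman.
- Keep a two-week status tick for the anemic symptoms, since that outcome is defined at that point.
- Re-head the fetal block to run from first dose to delivery, and state the same window in the outcome definition.
- State that fetal rates are computed in women pregnant at randomisation, and add a not-applicable option for the others.

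The cost is a revised form and one delivery-outcome contact for each pregnant woman. The Follow-Up section does not describe that contact, so it is a real addition, but it fits the planned period: entry at week 14 with delivery at week 40 is 26 weeks, about 6 months, against at least 10. No laboratory test is added, because SEUCR and lipids are already planned, and the sample size does not change.
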